### Strategies to improve adherence to interventions {11c}

There is no possibility to influence patients’ adherence to the intervention. Embolization of the MMA constitutes the only study intervention, which is solely performed by the clinical investigators.

### Relevant concomitant care permitted or prohibited during the trial {11d}

Except for the study intervention, patients in both groups are treated according to the currently established standard of care at the trial center (ukb). Any concomitant care as part of routine clinical practice is permitted.

### Provisions for post-trial care {30}

A proband cover for all patients participating in the study is contracted to compensate for trial-associated harm occurring within 5 years of trial participants’ final study visit.

### Outcomes {12}

#### Primary outcome

The primary outcome is cSDH recurrence up to 3 months after surgery. Recurrence is defined by one and/or both of the following criteria:Recurrent cSDH with at least the same volume (±10%) compared to baseline findingsRecurrent cSDH which requires surgery

Recurrence of cSDH is operationalized as a binary outcome (i.e., recurrence or no recurrence) during a follow-up period of 3 months.

#### Secondary outcomes

The following secondary outcomes will be assessed up to 3 months after surgery:Neurological deficits evaluated by the modified Rankin scale (mRS)Quantity and characteristics of recurrence-associated complicationsQuantity and characteristics of complications associated with endovascular embolization

The mRS [36] measures the degree of disability or dependence in the daily activities of people who have suffered a stroke or other causes of neurological disability. Scale values and interpretations are:0 = No symptoms.1 = No significant disability. Able to carry out all usual activities, despite some symptoms.2 = Slight disability. Able to look after own affairs without assistance, but unable to carry out all previous activities.3 = Moderate disability. Requires some help, but able to walk unassisted.4 = Moderately severe disability. Unable to attend to own bodily needs without assistance, and unable to walk unassisted.5 = Severe disability. Requires constant nursing care and attention, bedridden, incontinent.6 = Dead

#### Tertiary outcomes

The following tertiary outcomes are only addressed in a sub-sample of participants consenting to genetic analyses:Relationship between factor XIII deficiency (i.e., activity after cryopreservation <70%) and risk of cSDH recurrencePredisposition of genetic variants F13A1 rs2815822 and F13B rs12134960 for factor XIII deficiency

### Participant timeline {13}

Participants in the intervention and control groups will undergo five and four scheduled follow-up visits, respectively (Table 1):*−t*_1_ Screening and informed consent*t*_0_ Randomization*t*_1_ Baseline*t*_2_ Embolization (intervention group only, within 72 h after surgery)*t*_3_ Follow-up 1 month after baseline (± 1 week)*t*_4_ Follow-up 3 months after baseline (± 1 week)

**Table 1 Tab1:** Schedule of enrollment, interventions, and assessments

	Study period					
	Enrollment	Allocation	Post-Allocation			Close-Out
Time point	*−t*_*1*_	*t*_*0*_	*t*_*1*_	*t*_*2*_	*t*_*3*_	*t*_*4*_

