**Methods:**

MEMBRANE is an investigator-initiated, single-center, randomized controlled trial. Male, female, and diverse patients older than 18 years scheduled for surgical evacuation of a first cSDH will be assigned in a 1:1 fashion by block randomization to the intervention (surgery plus endovascular MMA embolization) or the control group (surgery alone). The primary trial endpoint is cSDH recurrence within 3 months of follow-up after surgery. Secondary endpoints comprise neurological deficits assessed by the modified Rankin Scale (mRS) and recurrence- or intervention-associated complications during 3 months of follow-up. Assuming a risk difference of 20% of rebleeding and surgical revision, a power of 80%, and a drop-out rate of 10%, 154 patients will be enrolled onto this trial, employing an adaptive O’Brien-Fleming approach with a planned interim analysis halfway.

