### Eligibility criteria {10}

#### Inclusion criteria

Patients scheduled for surgery by means of one or more burr hole trepanations during the first manifestation of a cSDH (unihemispherical or bihemispherical), as detected by CT or MRIAge ≥18 yearsWritten informed consent of the patient to participate in the trialLikely compliance of the participant in attending follow-up examination

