## Interventions

### Explanation for the choice of comparators {6b}

Patients assigned to the control group will be managed according to the current standard of care, i.e., neurosurgical evacuation of cSDH by burr hole trepanation and/or any surgical technique without specific added treatment.

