### Intervention description {11a}

Patients assigned to the experimental arm will undergo neurosurgical evacuation of cSDH by burr hole trepanation and/or any surgical technique plus endovascular embolization of the MMA (see Fig. 2).

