## Assignment of interventions: blinding

### Who will be blinded {17a}

Due to the surgical and interventional nature of trial modalities, blinding of both the immediately performing clinical investigators (i.e., neurosurgeons and interventional radiologists) and patients is almost impossible. While a sham procedure (i.e., placement of a transfemoral catheter and even infusion of a saline placebo) in the control group may be implemented, this is considered unethical as it exposes patients to additional harm without any possible benefit, given the primary endpoint.

Radiological experts evaluating baseline and follow-up CT scans after 1 and 3 months will be blinded to the randomly assigned treatment, assuring this is an observer-blinded trial.

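### Allocation appears to be released before the evacuation that both arms share, so the operating team can know the arm while operating; releasing it after surgery would close this avoidable route to bias

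*Protocol article*

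**What the plan says.** All references are to the protocol article.

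- **Order of events.** Participant timeline {13} places screening and consent first, then "Randomization*t*_1_ Baseline*t*_2_ Embolization (intervention group only, within 72 h after surgery". Neither the list nor Table 1 gives surgery a time point.
- **Status at assignment.** The abstract (Methods) says that patients "scheduled for surgical evacuation of a first cSDH will be assigned in a 1:1 fashion by block randomization". The inclusion criteria likewise admit "Patients scheduled for surgery by means of one or more burr hole trepanations during the first manifestation of a cSDH".
- **Release of the code.** Concealment mechanism {16b} holds the allocation back until screening is complete and the patient is cleared for entry. It does not mention the end of surgery.
- **Blinding.** Who will be blinded {17a} states that "blinding of both the immediately performing clinical investigators (i.e., neurosurgeons and interventional radiologists) and patients is almost impossible". The only blinded role is outcome reading: "Radiological experts evaluating baseline and follow-up CT scans after 1 and 3 months will be blinded to the randomly assigned treatment".
- **Technique.** The control arm receives "neurosurgical evacuation of cSDH by burr hole trepanation and/or any surgical technique without specific added treatment" and the experimental arm "neurosurgical evacuation of cSDH by burr hole trepanation and/or any surgical technique plus endovascular embolization of the MMA". Entry, however, requires planned burr hole surgery, and the exclusion criteria rule out primary craniotomy, primary craniectomy and bilateral burr holes.
- **Other care.** Section {11d} ties both arms to the standard of care at the centre and adds: "Any concomitant care as part of routine clinical practice is permitted".

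**The concern.** Embolization is the only study intervention (section {11c}), and it follows surgery. Until the evacuation is over, nothing needs to differ between the arms. If the surgeon already knows the arm, the thoroughness of evacuation, the choice among permitted techniques or the immediate aftercare could differ by arm, deliberately or not.

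The primary outcome is recurrence of the haematoma that this operation removes. A difference in how it was removed would be counted as an effect of embolization. More thorough surgery in controls would hide a benefit; more thorough surgery in the embolization arm would create or enlarge one. Blinded CT reading protects the measurement of volume but cannot undo a real difference in recurrence produced in theatre. Neither the modified intention-to-treat set nor the per-protocol set removes it.

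**Working it through.** **1. Does allocation precede surgery?** Three passages point the same way. Patients are assigned while surgery is scheduled (abstract). Eligibility is defined by a scheduled operation (inclusion criteria). Randomization (t0) precedes baseline (t1), and the volume criterion of the primary outcome compares a recurrence with baseline findings, which makes sense only if baseline is pre-operative. The order is a strong inference, because surgery itself is not placed in the schedule.

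**2. Can the operating team know the arm?** Section {16b} makes the code available once screening is complete. Section {17a} treats blinding of neurosurgeons as almost impossible. No passage withholds the arm from the theatre team until the operation ends. So they can know it; that they will is not stated.

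**3. Is that unavoidable?** No. Embolization comes up to 72 h after surgery, so the reason given in {17a}, the nature of the procedures, need not apply to the index operation.

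**4. The plan's sample size.** Inputs from Sample size {14}: 30% versus 10%, total alpha 5%, power 80%, 69 per group, 10% drop-out.

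- Pooled two-sided z-test: n = [1.96·√(2·0.20·0.80) + 0.8416·√(0.30·0.70 + 0.10·0.90)]² / 0.20² = (1.109 + 0.461)² / 0.04 ≈ 61.6, so 62 per group.
- Fisher's exact test at 5% has 80.0% power (79.97%) at 68 and 80.7% at 69 per group, so 69 reproduces on that basis.
- Enrolment: 138 / 0.9 = 153.3, rounded up to 154, as stated.

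This point does not depend on which test produced 69.

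**5. How sensitive is the result?** The documents give no effect of surgical technique on recurrence, so every shift below is assumed. Inputs: n = 69 per arm, the planned chi-square test, the final nominal level 0.0469 from section {20a}, interim look ignored. With x control and y experimental recurrences, p̄ = (x + y)/138 and z = [(x − y)/69] / √[2p̄(1 − p̄)/69]. The probability of declaring superiority is the sum of Bin(x; 69, p_C)·Bin(y; 69, p_E) over all pairs with x > y and two-sided p < 0.0469.

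| Scenario | Control | Experimental | P(superiority declared) |
|---|---|---|---|
| No embolization effect, no shift | 30% | 30% | 2.4% |
| Surgery alone lowers experimental risk | 30% | 28% | 4.2% |
| same | 30% | 26% | 7.2% |
| same | 30% | 24% | 11.6% |
| True effect, no shift | 30% | 10% | 85% |
| Surgery alone lowers control risk | 27% | 10% | 75% |
| same | 25% | 10% | 65% |

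One way to reach the 2, 4 and 6 point shifts: suppose two variants of the evacuation carry 20% and 40% risk and controls receive them equally often (0.5·20 + 0.5·40 = 30%). If the experimental arm receives the better variant 10, 20 or 30 points more often, its risk is 28%, 26% or 24%. With a 1.5-fold instead of a 2-fold ratio (24% and 36%), the risks are 28.8%, 27.6% and 26.4%, and false superiority is 3.4%, 4.7% and 6.5%.

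**The case against.** **The protocol nowhere says that the surgeon operates knowing the arm.** Correct. Surgery is missing from the schedule and the flowchart is not shown. One exclusion criterion, that angiography cannot be performed within 72 h after surgery, might even suggest that screening is not closed until then. This limits confidence to moderate. It does not remove the point, because no passage shown prevents the knowledge.

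**Technique is not really open.** Largely fair. A reader might infer from the arm descriptions that surgeons may do anything, but entry requires planned burr hole surgery, several primary operations are excluded, one centre's standard applies, and the wording is the same in both arms. What stands is a conflict between sections {6b} and {11a} and the eligibility criteria. Even within burr hole surgery, thoroughness and aftercare can vary.

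**The size is assumed at every step.** Correct. The technique mix, the risk ratio and the imbalance have no source in the documents, and in the mildest case shown false superiority moves only from 2.4% to 3.4%. The figures show sensitivity and do not forecast bias.

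**Randomizing to a strategy before surgery is legitimate.** It is. A reader might also infer that intervention patients who cannot be embolized damage the trial. Under the as-randomized analysis they belong to the comparison of strategies. If 5% were not embolized (experimental risk 0.95·10 + 0.05·30 = 11%), power would still be 80.5%. That argument is not needed here.

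**Conclusion.** The point holds as an avoidable opening for performance bias. On the natural reading, allocation precedes an operation shared by both arms, and nothing shown keeps the arm from the team that performs it. The justification for not blinding neurosurgeons need not extend to that operation.

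The documents do not support the stronger conclusion that surgeons will operate differently by arm, that the bias favours embolization, or that the primary comparison is invalid. Direction and size are unknown. The illustrations (false superiority of 4.2% to 11.6% against 2.4%; power of 75% or 65% against 85%) rest entirely on assumed shifts of 2 to 6 points in the experimental arm and 3 or 5 points in controls. They show only that modest differences in surgical outcome would matter at 69 per arm.

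Severity: should be fixed. Confidence: moderate, because both the order of events and the surgeon's knowledge of the arm are inferred.

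**What to change.** 1. Keep consent before surgery. Release the secuTrial allocation only after the evacuation is completed and eligibility is confirmed, including that angiography is feasible within the existing 72 h window. If earlier randomization is needed for logistics, withhold the result from the operating team until surgery ends.
2. Show surgery as a time point in the timeline and Table 1, and state where t0 and baseline stand relative to it.
3. In section {17a}, separate the index evacuation, for which the team can be kept unaware of the arm, from the embolization and later care.
4. Reconcile the open wording on surgical technique in sections {6b} and {11a} with the inclusion and exclusion criteria. Which surgical rule applies is for the investigators to decide.

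**Cost.** An amendment with written sign-off and, if necessary, ethics approval (section {25}), and a changed release point in secuTrial. The angiography slot is booked later and part of the 72 h window is used. Some consented patients may prove ineligible after surgery and never be randomized. The target of 138 evaluable and 154 enrolled patients is unchanged. The article puts the planned start of recruitment one day after the protocol version date (20 and 19 April 2022), so the change may reach only patients not yet randomized.

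**What it leaves open.** The decision to re-operate, which is part of the primary outcome, would still be taken by unblinded clinicians.

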**Assessments**						
Demographics, medical history, laboratory data			X			
Neurological tests			X		X	X
Computed tomography			X		X	X
Complications				X	X	X

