## Statistical methods

### Statistical methods for primary and secondary outcomes {20a}

The primary outcome, i.e., reduction in cSDH recurrence through the experimental, surgical plus endovascular treatment, compared to surgery alone, will be analyzed using a chi-square fourfold test for independent samples. The two-sided significance level *α* is set at 5% and the power at 80%. Superiority of the experimental intervention over control is assumed, if the resulting *p*-value is below the nominal significance level of 0.00031 at the time of interim analysis (prompting early trial termination), or the nominal significance level of 0.0469 at the time of final analysis.

Secondary categorical outcomes will be investigated by the Cochran-Mantel-Haenszel (CMH), chi-square, or Fisher’s exact test (if one of the cell frequencies is <5). Recurrence-associated complications, complications associated with endovascular embolization, and (serious) adverse events will be expressed as absolute and relative frequencies.

Exploratory analyses will be performed for the distribution of genetic variants and their correlation (by Pearson’s *phi*-coefficient) with factor XIII deficiency (<70%) across the entire cohort without stratification for the type of intervention. The closer the *phi*-coefficient to 1 or -1, the stronger the association (or predisposition) between genetic variants and factor XIII deficiency. Advanced analyses will be performed to study the association between heterozygous, homozygous, and wild type variants, factor XIII activity, and cSDH recurrence.

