### Adverse event reporting and harms {22}

All SAEs reported by study participants or observed by an investigator within the study period must be documented in the eCRF. SAEs are any undesirable sign, symptom, or medical condition whichIs fatalIs acutely life-threateningRequires or prolongs inpatient hospitalizationResults in persistent or significant disability/incapacityConstitutes a congenital anomaly or birth defect (not applicable, pregnancy excludes from study participation)

The principal investigator will be informed immediately about the onset of a SAE and must decide whether the participant shall be excluded from or remain in the study. The likelihood of a causal relationship between the individual trial intervention and SAE will be investigated further, and patients will be observed until the SAE resolves or a stable condition is reached.

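### Table 1 schedules complications at t2, a visit only the embolization arm has, so comparisons of early non-serious complications are open to differential ascertainment

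*Protocol article*

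**What the plan says.** In the protocol article, Participant timeline {13} states: "Participants in the intervention and control groups will undergo five and four scheduled follow-up visits, respectively". The only time point marked for one arm is t2, described as "Embolization (intervention group only, within 72 h after surgery". The next time point, t3, is "Follow-up 1 month after baseline (± 1 week" and applies to both arms, as does t4 at 3 months.

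Table 1 has one row labelled "Complications". It is marked at t2, t3 and t4 and is not divided by type of complication. Scheduled CT is marked at t1, t3 and t4.

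Four other sections bear on how much this matters:

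- Secondary outcomes lists recurrence-associated and embolization-associated complications under one window: "The following secondary outcomes will be assessed up to 3 months after surgery".
- Plans for assessment and collection of outcomes {18a} lists cerebral edema and cerebral infarction as recurrence-associated. It lists ten items as intervention-associated, acute renal failure among them, and allows free-text entries for anything else.
- Adverse event reporting and harms {22} requires that "All SAEs reported by study participants or observed by an investigator within the study period must be documented in the eCRF".
- Statistical methods {20a} plans absolute and relative frequencies for both kinds of complication and for adverse events. A more general sentence assigns Cochran-Mantel-Haenszel, chi-square or Fisher tests to secondary categorical outcomes.

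**The concern.** If one arm is asked about complications early and the other is first asked a month later, the arms can show different counts with the same true risk. Short-lived, non-serious events are the ones most easily lost by 1 month. Because the row is not split, the t2 entry covers events that either arm can have (edema, infarction, free-text events) as well as those that belong to the catheter procedure. The blinding section names only the CT readers as blinded, and t2 is by its nature an unblinded contact.

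Complications are a secondary objective. The introduction gives effectiveness and safety as the aim of the trial, and the discussion calls for a benefit-to-risk evaluation against standard surgery. Frequencies printed by arm will be read as a comparison even if no test is run. An excess in the embolization column could then be a real effect, the extra look, or both, and analysis could not reliably separate them.

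**Working it through.** The plan gives no figure to reproduce here. The check sets the schedule against the outcome and safety sections, then illustrates the possible size.

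**First scheduled complication assessment**

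- Embolization arm: t2, within 72 h after surgery.
- Control arm: t3, 1 month ± 1 week after baseline, so roughly week 3 to week 5.

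**What can be affected**

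- Serious events: no gap in the rule. Documentation covers the whole study period and is not tied to a visit or an arm.
- Embolization-associated items: the plan defines no control counterpart, so there is no comparison to distort. Recording them at t2 is natural.
- Recurrence-associated and free-text events that are not serious: Table 1 is the only scheduled collection point shown, and it gives one arm an extra early look. No scheduled CT falls in that window in either arm.
- Primary endpoint: not touched by this row, since scheduled CT is the same in both arms.

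**Illustration of size**

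The document gives none of these inputs; all are assumed:

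- *p*: true complication risk, equal in both arms.
- *e*: share of events that arise early.
- *d*: chance that an early control event is still recorded later, at t3 or t4 or as a serious event.
- Early events in the embolization arm are all recorded at t2.

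Observed risk, embolization arm = *p*.

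Observed risk, control arm = *p*(1 − *e*) + *p·e·d*.

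Apparent risk ratio = 1 / [1 − *e*(1 − *d*)], which does not depend on *p*.

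Example with *p* = 10%, *e* = 25%, *d* = 80%: control risk = 0.10 × 0.75 + 0.10 × 0.25 × 0.80 = 0.075 + 0.020 = 0.095, and the ratio is 0.10 / 0.095 = 1.05.

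| *e* | *d* | Control risk observed (*p* = 10%) | Spurious difference (points) | Apparent risk ratio |
|---|---|---|---|---|
| 25% or 50% | 100% | 10.0% | 0 | 1.00 |
| 25% | 80% | 9.5% | 0.5 | 1.05 |
| 50% | 80% | 9.0% | 1.0 | 1.11 |
| 25% | 50% | 8.75% | 1.25 | 1.14 |
| 50% | 50% | 7.5% | 2.5 | 1.33 |
| 25% | 0% | 7.5% | 2.5 | 1.33 |
| 50% | 0% | 5.0% | 5.0 | 2.00 |

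With 77 patients per arm and *p* = 10%, the rows with 50–80% recovery mean 77 × 0.10 = 7.7 recorded events against 77 × 0.095 = 7.3 down to 77 × 0.075 = 5.8. The *d* = 0 rows are a bound only: they would need no later recording of early control events at all, which the serious-event rule and the common visits make implausible.

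**The case against.** The case on the other side is substantial.

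- **Both arms are observed.** The complication outcomes run from surgery to 3 months, t3 and t4 are common, and serious events are recorded throughout in everyone. A reader might infer from Table 1 that early complications are looked for in one arm only; these provisions rule that out. This stands.
- **Many of the named events would be serious.** The definition includes events that prolong hospitalization, threaten life or disable. Symptomatic edema or infarction soon after cranial surgery would usually qualify. This stands and narrows the gap to milder and free-text events. Recurrence-associated events also presuppose a recurrence, so few may fall before t2.
- **Acute renal failure is not a shared item in this plan.** It is listed as intervention-associated, so it cannot serve as an example of a shared complication. This stands.
- **No between-arm test is named for complications.** They are planned as frequencies. This stands in part: the general sentence on secondary categorical outcomes could reach recurrence-associated complications, and frequencies shown by arm invite comparison anyway.
- **Nothing says that t3 relies on patient recall.** In a single-center trial the chart could be consulted. This stands as a possibility, but no section says that the 1-month form must recover control events from the first 72 h.
- **t2 is the embolization itself.** It can fall at any time within 72 h, and events after it wait for t3 in both arms. This stands; the assumption of full early capture in the embolization arm is generous.
- **Form-level detail belongs in the full protocol.** This is true of the eCRF items. The schedule itself, however, is stated in the article, and it is unequal.

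**Conclusion.** The unequal schedule is real: one undifferentiated complication assessment at a visit that only the embolization arm has, with controls first assessed at about 1 month. The consequence is a potential for differential ascertainment of early, non-serious recurrence-associated and free-text complications. It is not a demonstrated bias. Any error would count against embolization.

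The apparent risk ratio is 1.00 if all early control events are recovered later, and about 1.05 to 1.33 if 50–80% are recovered and 25–50% of events are early. These inputs are assumptions, so neither the size nor the presence of an effect can be settled from the document.

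A reader might go further and say that the safety comparison is biased, or that embolization would look 1.4 to 2 times as harmful. Those ratios (1/0.7 and 1/0.5) arise only for early non-serious events taken alone, with assumed capture of 70% or 50% in controls. They leave out all events recorded equally in both arms and the case of full recovery. The document does not support them as a statement about the trial's complication results. The primary endpoint is unaffected.

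**What to change.** Choose one of two changes to Table 1:

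1. Add a chart-based complication entry for controls at 72 h after surgery, on the same eCRF page as the embolization arm, with both arms' entries covering the same window from surgery; or
2. Keep t2 as it is, but label its complication entry as limited to procedure-related items.

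Under either option, state that arms are compared only on complications that can occur in both and are collected at the same time points. Procedure-specific items (vessel dissection, particle or coil dislocation, puncture-site events) are then reported descriptively in the embolization arm.

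The first option costs one additional eCRF page for about 77 control patients, with no extra procedure or imaging. The second needs no added data collection, but gives up the early look at shared events. Trial status says that recruitment had not begun at submission, so either could be made by amendment. The change is best made early, because events missed in the first days cannot reliably be recovered by analysis.
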